### Purpose of the study

This study will operate a RCT including neuromuscular training exercise and taping in patients with PFPS to determine the following:whether neuromuscular training exercise is effective for treating PFPS;whether neuromuscular training exercise has more advantageous effects than taping and health education for PFPS patients;the adverse effects of neuromuscular training exercise.

### Study design

We will design a single-blind RCT to compare neuromuscular training exercise with taping and health education (Fig. 1). We will recruit and investigate a total of 120 patients with PFPS from Shanghai Shangti Orthopedic Hospital and Shanghai University of Sport, Shanghai City, China, and different running teams from Shanghai.

**Fig. 1 Fig1:**
[figure not shown]
*Flow diagram* showing neuromuscular training exercise for PFPS patients

Before starting the study, all individuals will fill in a questionnaire including basic personal information, such as age, educational background, and injury history. The questionnaire will also include a section on pain intensity (visual analog scale [VAS]) and knee function (Anterior Knee Pain Scale [AKPS]). Before inclusion, informed consent will be obtained from all participants.

All individuals who conform to the study will be randomly assigned in a 1:1:1 ratio by a computer. Afterward, patients with PFPS will be distributed to the control group (health education), first intervention group, (neuromuscular training exercise), or the second intervention group (taping). The whole study will last for six months, which includes three months of intervention and another three months of follow-up period without intervention.

The assessments will be conducted before the intervention, at six weeks, at three months, and at six months.

### Participants

#### Inclusion and exclusion criteria

The participants should meet the following requirements: (1) aged 20–50 years; (2) running more than half a year and pain lasting longer than one month; (3) anterior or retropatellar knee pain from at least two of the following: prolonged sitting; climbing stairs; squatting; running; kneeling; and hopping/jumping; (4) anterior knee pain is not caused by trauma; (5) the patellofemoral joint extrusion test is positive. The exclusion criteria are as follows: (1) meniscus injury; (2) laxity of articular ligament; (3) pressure pain on the tibial tract, the goose foot tendon, and patellar ligament; (4) effusion of knee joint; (5) history of patellar dislocation; (6) severe cardiovascular or osteoporosis, progressive neurological deficits; (7) pregnancy women or lactating women; (8) VAS score (in the range of 1–10) > 8; and (9) VAS score (in the range of 1–10) < 3.

### Withdrawal criteria and management

PFPS patients will be asked or be allowed to quit the study if:they have such a demand;they are diagnosed with a severe disease, such as cardiovascular disease;they obtain a side effect because of treatment.

### Interventions

All the groups will receive basic information and intervention details individually before they enter the study. The individuals will be required to fill in forms to record the durations and times of intervention. The patients will need to keep their normal lifestyle and avoid taking any other rehabilitation treatments.

### Neuromuscular training exercise group

The participants will perform the neuromuscular training exercise, including the quadriceps femoris and gluteal muscle strength training, balance training (Fig. 2), and knee proprioceptive sense training. The muscle strength training includes five different exercise training movements (Fig. 3). All individuals should come to the clinical center three times a week. The whole exercise routine has three parts: warm up for 5 min; neuromuscular training exercise for 40 min; and muscle stretching for 5 min. The physical therapist will give the participants a guideline for each type of movement. The training exercise regimen will be different according to the period and participants’ body condition. We will normally increase the training intensity every two weeks by expanding the training time and convert to a more difficult exercise (Figs. 2 and 4), such as deep squats with different angles and using different stretching force elastic bands (blue: high intensity, yellow: low intensity).

**Fig. 2 Fig2:**
[figure not shown]
Balance training exercise: (**a**) knee flexion at 30°; (**b**) knee flexion at 60°

**Fig. 3 Fig3:**
[figure not shown]
**a–e** Muscle strength training in five different exercises

**Fig. 4 Fig4:**
[figure not shown]
Different stretching force elastic bands: (**a**) low intensity; (**b**) high intensity

### Taping group

A certified physical therapist will tape participants with a Y-shaped tape (Fig. 5) from the lower edge of the patella to the middle segment of the quadriceps femoris and an I-shaped tape according to Kenzo Kase’s Kinesio taping manual. The tape therapy will last for three months and all individuals should come to the clinical center three times a week.

**Fig. 5 Fig5:**
[figure not shown]
**a** Y-shaped taping. **b**, **c** Y- and I-shaped taping

### Health education group

The participants in this group will attend sessions on protecting the knee from injury while they are running or in the daily life for once a week. In addition, we will use the Internet to broadcast some articles about the PFPS concept and how to deal with it. The health education sessions will also last for three months.

### Outcome measures

#### Primary outcome measures

We will use the VAS scores to evaluate pain intensity. Normally, the VAS comprises a horizontal line with a length of 100 mm and a pain scale of 0–10, where the score “0” means no pain and “10” unbearable pain. The pain intensity is described by the patient who points to a number from the line [27].The knee function self-report questionnaire will be administered. The results will be evaluated using the AKPS. The Chinese translated version of the AKPS is a reliable and valid questionnaire for patients with PFPS [28–30]. It is a 13-item knee-specific self-report questionnaire used to record a patient’s reaction to six different activities, which may have specific connections with PFPS syndrome. The AKPS is used to record the duration of symptoms and which limb(s) is/are affected. Its full score is 100 and lower scores mean significant pain or severe knee function.The adverse events, which have correlations with neuromuscular training exercise and taping, will be recorded.

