**Methods:**

We will operate a prospective, single-blind, randomized controlled trial of 60 patients with patellofemoral pain. Individuals will be indiscriminately assigned to two intervention groups and a health education group. The neuromuscular training exercise which includes the muscle strength training, balance training and knee joint proprioception training, and taping group will use “Y” and “I” type taping on the participants three times a week for three months. The health education group will be given education lectures once each week and which last for three months. The primary outcome measures include the adverse events, visual analog scale for pain, and Anterior Knee Pain Scale Index, which is a knee function self-report questionnaire to evaluate the function of the knee especially for PFPS patients. The secondary outcome measures are the muscle strength and endurance of knee joint flexion and extensor muscles, knee joint proprioception, muscle thickness of the quadriceps femoris, knee function ability, and quality of life. We will manage the intention-to-treat analysis for individuals who will withdraw from this study.

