### Statistical analysis

Statistical analyses will be carried out using SPSS 22.0 and Microsoft Excel 2012 software. Data will be represented as mean ± standard deviation. We will use two-way repeated measures analysis of variance (group × time) to compare the effect of neuromuscular training exercise group with the taping and control groups, including the primary and secondary outcomes. The intention-to-treat analysis will be conducted if individuals are lost to follow-up. The t-test will be carried out to compare the changes in measures within groups. Statistical significance will be considered at *P* value < 0.05.

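### Adverse events are a primary outcome, but their recording is worded around exercise and taping only, which biases comparison with health education, and the blanket ANOVA sentence does not suit event data

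*Protocol article*

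**What the plan says.** The abstract puts adverse events among the primary outcomes: "The primary outcome measures include the adverse events, visual analog scale for pain, and Anterior Knee Pain Scale Index". The section Primary outcome measures repeats this and gives the only recording rule: "The adverse events, which have correlations with neuromuscular training exercise and taping, will be recorded". Health education, the third randomised arm and the control, is not named there.

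The section Purpose of the study lists as its third aim "the adverse effects of neuromuscular training exercise". This concerns one arm and is not worded as a comparison.

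The section Statistical analysis begins its data handling with "Data will be represented as mean ± standard deviation" and continues: "We will use two-way repeated measures analysis of variance (group × time) to compare the effect" of training against taping and control, "including the primary and secondary outcomes". It makes no exception for adverse events and names no method for counts or proportions.

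**The concern.** Two separate problems follow.

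**Collection.** Participants in the health education arm receive neither exercise nor tape. If an event must be linked to one of these to be recorded, that arm can contribute few events or none. Background events are nevertheless plausible in every arm: the eligibility criteria require people who run and who have knee pain within a VAS band, and the Interventions section asks them to keep their usual lifestyle. Contact also differs, with three clinic visits a week in the active arms and one session a week in health education. Background events that pass the filter in the exercise arm then have no counterpart in the control arm, and they appear as harm from exercise.

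**Analysis.** A group × time ANOVA summarised by mean and SD is made for roughly continuous measurements such as VAS or AKPS. Adverse events at this sample size are sparse counts or yes/no data.

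At stake is the safety statement on exercise, which is both a primary outcome and a stated aim.

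**Working it through.** **Plan figure.** The article gives no event rate and no sample-size reasoning for adverse events, so there is nothing to reproduce. Its one design figure, 60 participants, was derived for an ANOVA effect size and does not bear on this point.

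**Inputs.**
- 20 per arm (Sample size estimation), allocated 1:1:1 (Study design).
- Two-sided significance level 0.05 (Statistical analysis).
- True proportion of participants with an event, p: *assumed*, 5% to 30%, equal in the exercise and health education arms, so that there is no true difference.
- Filter scenario, a limiting case: every event in the exercise arm is recorded and none in health education.
- Fisher's exact test, chosen for illustration; the article does not name it.

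**Step 1: how many events against 0/20 give p < 0.05?** For a events in 20 against 0 in 20, the two-sided Fisher p-value is 2 × C(20,a) / C(40,a).
- a = 4: 2 × 4,845 / 91,390 = 0.106.
- a = 5: 2 × 15,504 / 658,008 = 0.047.

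Five events in the exercise arm are enough.

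**Step 2: how often does that happen with no true difference?** Under the filter scenario, P(false significance) = P(X ≥ 5) with X ~ Binomial(20, p). With complete recording, both arms are Binomial(20, p), and the probability is summed over all pairs of counts with p < 0.05.

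| Assumed true rate, both arms | Control events unrecorded | All events recorded | Expected false difference when control events are unrecorded |
|---|---|---|---|
| 5% | 0.3% | 0.2% | 5 points |
| 10% | 4.3% | 1.2% | 10 points |
| 20% | 37.0% | 2.3% | 20 points |
| 30% | 76.3% | 2.5% | 30 points |

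The last column is p − 0. It shows bias in the estimate even where the test rarely reaches significance.

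**Step 3: sensitivity to the limiting case.** If only a fraction q of exercise-arm events passes the filter, p is replaced by q × p. A true rate of 20% with half recorded gives 0.5 × 20% = 10%, and the false-positive risk falls from 37.0% to 4.3%; the expected false difference is then 10 points. The size therefore depends on how many background events are attributed to exercise.

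**Step 4: mean ± SD for a yes/no event.** The mean is p, and the SD is about √(p(1 − p)), fixed by p. At an assumed 10%, √(0.10 × 0.90) = 0.30, so the summary reads 0.10 ± 0.30, with limits that include negative values and no information beyond the proportion. An arm with no recorded events has mean 0 and SD 0, so the arms cannot share a common variance as ANOVA assumes. The first of the four assessments precedes the intervention, so no treatment-related event can occur at that time level.

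**The case against.** Several stronger readings are tempting, and the article does not support them.

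- *The control rate is zero by definition.* The commas around the relative clause allow a descriptive reading instead of a filter, and the abstract lists adverse events without restriction. This stands. It lowers certainty about what will be done, but even the descriptive reading ties adverse events to exercise and taping and leaves control-arm events unaddressed.
- *Someone who knows the arm decides what is recorded.* The article names no assessor and no causality judgement, and says only that the trial is single-blind.
- *No valid between-arm comparison is possible.* Events linked to treatment are recorded in both the exercise and taping arms, and their proportions could be compared, although attribution may differ by arm. An unsuitable test can also be replaced.
- *The third aim cannot be answered.* That aim is descriptive and concerns the exercise arm. It can be answered descriptively; what is lost is the background rate against which to read it.
- *Small arms prove the point.* With 0/20, the exact two-sided 95% upper limit is 1 − 0.025^(1/20) = 16.8%, and power for event comparisons is low. Both come from 20 per arm and would remain after any correction, so they do not measure this defect.

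It is also fair to say that pain worsening still present at an assessment would show in the VAS, which is a primary outcome for every arm. This covers one kind of event only.

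Condensation into an article is not an answer here. A fuller document would have to depart from the recording and analysis sentences as published to remove the problem.

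**Conclusion.** The point holds in a limited form. The recording rule for a primary outcome covers exercise and taping and does not cover health education. Under the filter reading, comparison with that arm is biased against the active arms. In the limiting case, false significance occurs in about 37% to 76% of trials at assumed true rates of 20% to 30%, against about 2% with complete recording. At 5% to 10% it is 0.3% to 4.3%, with the estimate still biased. These figures rest on assumed rates, 20 per arm, Fisher's test and full recording in the exercise arm.

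The between-arm use of adverse events follows from their primary status together with the blanket analysis sentence, not from the stated aim. That sentence assigns them a method that does not fit, whichever way the recording rule is read. Both sentences should be corrected. Confidence in the core is good; confidence that the rule operates as a strict filter is moderate.

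**What to change.** 1. Record all adverse events in all three arms, whatever the presumed cause, using the same prompt at each scheduled assessment so that unequal contact does not drive the counts.
2. Grade relatedness to the intervention afterwards, as a separate field.
3. Exempt adverse events from the ANOVA and mean ± SD sentences. Report, per arm, the number of participants with at least one event and the number of events, with exact 95% confidence intervals. If arms are compared, use an exact or count method.

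Moving adverse events from the primary outcomes to a separate safety outcome is optional and not needed for the correction.

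The cost is one added question on the assessment form and revised wording; treatment and sample size do not change. The Trial status section says that recruitment is in progress, so control-arm events before the change may not be recoverable. The report should state the date of the change and which participants were affected.

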#### Secondary outcome measures

The quadriceps femoris strength and endurance indexes will be tested using the CON-TREX multijoint isokinetic test and training machine (CMV AG, Dübendorf, Switzerland). The maximum concentric contractions for knee flexors and extensors of individuals will be recorded at different angular velocities of 60°/s, 120°/s, and 180°/s. The muscle endurance index will be obtained according to the ratio of the work done during the last five contractions over the first five contractions. The parameters will be recorded as peak torque (Newton-meters), peak torque/body weight, power output (power) in watts, and work (work) in joules [20].The knee joint proprioception sense ability will also be evaluated using the CON-TREX multijoint isokinetic test and training machine. The individuals will be asked to move to a random reference position, hold this position for 3 s, and then repeat from the neutral position to the reference position. Next, the participants will find the nearest position and will keep this position so that the assessor can measure the position and angle. The knee joint proprioception test will be repeated three times and the final results will be averaged. A high absolute error means poor proprioceptive sense [31].The muscle thickness of the quadriceps femoris will be determined. We will use the portable musculoskeletal ultrasonic instrument (M7 Super Series, Mindray, USA) to evaluate four different muscles: rectus femoris, vastus intermedius, vastus lateralis, and vastus medialis. The methods we will follow are based on the studies by Giles [32, 33].We will use three tests to evaluate the knee joint function: anteromedial lunge test; step-down test (left and right); and balance-and-reach test. These tests have good reliability and can better reflect the function of knee joint [34].Quality of life will be evaluated using the Short Form 36 (SF-36) health survey. The survey is divided into eight different parts: vitality; physical functioning; bodily pain; general health perceptions; physical role functioning; emotional role functioning; social role functioning; and mental health (the psychometric properties). The score of SF-36 is from 0 (worst) to 100 (best) [35].

### Statistical analysis

Statistical analyses will be carried out using SPSS 22.0 and Microsoft Excel 2012 software. Data will be represented as mean ± standard deviation. We will use two-way repeated measures analysis of variance (group × time) to compare the effect of neuromuscular training exercise group with the taping and control groups, including the primary and secondary outcomes. The intention-to-treat analysis will be conducted if individuals are lost to follow-up. The t-test will be carried out to compare the changes in measures within groups. Statistical significance will be considered at *P* value < 0.05.

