### Hypothesis

The neuromuscular training exercise and taping both have a positive effect on the treatment of PFPS.The neuromuscular training exercise has a higher advantage than taping and health education in treating PFPS patients.

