## Methods

### Sample size estimation

According to the previous studies, the effect size of Kujala Patellofemoral Scale is in the range of 0.34–0.54. Pain intensity effect size is in the range of 0.45–0.56 [2]. In this study, we used G-Power Software: F-test, ANOVA: one-way repeated measures (version 3.1.9.2) with the following parameters: effect size = 0.3; test level = 0.05; test efficacy = 0.95; group numbers = 3, number of measurements = 3. The total sample size of this study should be a minimum of 60 participants in the three groups, or 20 participants in each group.

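### The only between-group test named, an omnibus group × time ANOVA, cannot show that training beats taping or that it beats education; two baseline-adjusted contrasts would

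*Protocol article*

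**What the plan says.** The Hypothesis section states that "The neuromuscular training exercise has a higher advantage than taping and health education in treating PFPS patients". The Purpose of the study section repeats this as an aim, to determine "whether neuromuscular training exercise has more advantageous effects than taping and health education for PFPS patients".

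The Statistical analysis section gives a two-way repeated measures ANOVA (group × time) as the way "to compare the effect of neuromuscular training exercise group with the taping and control groups, including the primary and secondary outcomes". The only other test is not a comparison of arms: "The t-test will be carried out to compare the changes in measures within groups". The section names no pairwise contrast, no time point for the comparison and no baseline covariate.

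On visits, the Study design section says: "The assessments will be conducted before the intervention, at six weeks, at three months, and at six months". The period covered is "three months of intervention and another three months of follow-up period without intervention". The Sample size estimation section, however, enters "effect size = 0.3; test level = 0.05; test efficacy = 0.95; group numbers = 3, number of measurements = 3". The article does not say which visits form the time factor of the ANOVA.

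**The concern.** The plan states a test and the comparison that test is meant to deliver, and the two do not match. A group × time interaction across three arms is significant when any two arms have different time profiles. It does not say which arms differ, in which direction or at which visit. A difference between taping and education alone would trigger it, as would one that appears only after the intervention has stopped.

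The Discussion already anticipates a conclusion that training does more good than education and taping. If the named test is read as the evidence for that conclusion, a significant result could be reported as support when training is no better than one of its comparators.

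A second, smaller issue is baseline. VAS and AKPS are collected before the intervention, but the plan names no adjustment for them.

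**Working it through.** **Inputs from the article.** Three arms, 1:1:1, 20 per arm (Sample size estimation; Study design). Four assessments, the first before the intervention (Study design). Significance level 0.05 (Statistical analysis). The Study design section also mentions 120 patients; I use 20 per arm, and the equality in step 3 holds for any number per arm.

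**Assumed, because the article does not give them.** SD 1 at every visit, compound symmetry with correlation ρ = 0.3, 0.5 or 0.7, and baseline as a level of time. An arm that works gains d = 0.8 SD over one that does not: nothing at baseline, half at 6 weeks, all of it at 3 and 6 months.

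**Step 1: the plan's own figure.** The total of 60 cannot be reproduced uniquely, because the correlation and the effect tested (between, within or interaction) are not given. With three measurements and ρ = 0.5 the stated inputs give 39 (interaction), 33 (within) or 120 (between). Sixty appears for the interaction at ρ = 0.2 (power 0.959) or for the within effect at ρ = 0 (power 0.954). The sample size therefore does not show which effect was meant to carry the conclusion. The point below does not rest on it.

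**Step 2: degrees of freedom.** Interaction (3 − 1)(4 − 1) = 6; error 57 × 3 = 171.

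**Step 3: noncentrality.** λ = n × (sum of squared interaction effects)/(1 − ρ).

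- Time part: the profile 0, 0.5, 1, 1 has mean 0.625. The squared deviations sum to 0.390625 + 0.015625 + 0.140625 + 0.140625 = 0.6875.
- Group part, one arm of three works: (2/3)² + 2(1/3)² = 2/3.
- Group part, two arms of three work equally: 2(1/3)² + (2/3)² = 2/3, the same.
- Hence λ = 20 × 0.6875 × (2/3) × 0.64/(1 − ρ) = 5.867/(1 − ρ), which is 8.38, 11.73 and 19.56.

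The noncentral F on 6 and 171 df then gives:

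| Truth | Training vs taping | Training vs education | P(significant), ρ = 0.3 / 0.5 / 0.7 |
|---|---|---|---|
| Only training works | better | better | 0.54 / 0.71 / 0.92 |
| Only taping works | worse | equal | 0.54 / 0.71 / 0.92 |
| Training and taping work equally | equal | better | 0.54 / 0.71 / 0.92 |

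The test cannot tell these rows apart, and only the first is the hypothesis.

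**Step 4: if baseline is not a time level.** The interaction then has no information on a constant post-baseline effect (rejection probability 0.05). The group main effect is still a non-directional test on 2 df across three arms. The mismatch with the hypothesis remains.

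**Step 5: baseline adjustment.** For one contrast at one visit with equal variances, the per-arm variance is 2(1 − ρ) for change from baseline and 1 − ρ² with baseline as covariate. The ratio is (1 + ρ)/2 = 0.65, 0.75 and 0.85, a reduction of 35%, 25% and 15%.

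**Step 6: power when training alone is better by 0.56 SD.** This is the top of the pain range in Sample size estimation, read here as a standardised mean difference, with the same time profile.

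- Omnibus interaction: λ = 20 × 0.6875 × (2/3) × 0.3136/(1 − ρ) = 4.11, 5.75 and 9.58; power 27%, 37% and 60%.
- One baseline-adjusted 3-month contrast: noncentrality 0.56/√(2(1 − ρ²)/20) = 1.86, 2.04 and 2.48; power about 45%, 51% and 67%.
- Both contrasts significant, by simulation: about 28%, 35% and 53%.

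**The case against.** The strongest reply is that this is a condensed article. Follow-up comparisons, the coding of time and covariates are often left to a full protocol or SAP, and the text does name the arms to be compared. Nothing says that superiority will be declared from the F-test alone. This stands in part: a fuller document may name pairwise contrasts, and a reader should not infer that the investigators intend to claim superiority from the omnibus p-value. What remains is that the article itself offers the ANOVA as the comparison of training with the other two arms, and the ANOVA does not make that comparison.

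Two further objections also stand.

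- Baseline as a time level is an inference from the four visits. The three measurements in the sample size calculation leave it open, and the figures in steps 3 and 6 depend on it. The mismatch does not (step 4).
- The interaction test is valid in a randomised trial. The 35%, 25% and 15% reductions are measured against a between-group change-score contrast that the plan does not name, so they are not losses of the planned test.

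It is tempting to go further and say that the plan would miss a real training benefit more often than the alternative. Step 6 does not support that. One adjusted contrast has more power than the omnibus test. Requiring both, which the hypothesis needs, is about level at ρ = 0.3, slightly lower at 0.5 and lower at 0.7. The omnibus test also addresses a different hypothesis, so the two powers are not like for like.

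**Conclusion.** The concern holds as a mismatch between question and test. The one between-group analysis named is non-directional and does not separate training versus taping from training versus education. Under the stated assumptions it is significant with probability 0.54 to 0.92 in situations where training is no better than one of its comparators, exactly as often as when the hypothesis is true. The equality is algebraic and holds for any number per arm, correlation or effect size under compound symmetry. The probabilities themselves depend on the assumed 0.8 SD effect, its time profile, the correlation range and baseline being a time level.

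Baseline adjustment improves the precision of each single-visit contrast relative to change from baseline, by 15% to 35% of the variance over the correlations considered. No general gain in power is claimed. The data would remain usable, so this should be corrected, but it does not undermine the trial.

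**What to change.** For VAS and AKPS, state as the primary analysis two planned contrasts, training minus taping and training minus education, at one named time point. Estimate them from a model of the post-baseline visits with the baseline score as covariate and with group, visit and group × visit as factors. Report each with a 95% CI, and claim superiority over both comparators only if both contrasts are significant. The group × time test can stay as a supporting analysis. State also which visits form the time factor.

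Three months, the end of the intervention, is a reasonable time point, but the article does not dictate it and the investigators should choose.

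The cost is wording only: no new data or visits. The other time points become secondary; with 3 months chosen, this includes the 6-month result on durability. Power for the joint claim is modest at 20 per arm (about 28% to 53% at 0.56 SD), and the sample size section should be rechecked against these contrasts.

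### Intention-to-treat is made conditional on loss and paired with a repeated-measures ANOVA that, in its standard form, needs complete data, while side-effect withdrawals may leave follow-up altogether

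*Protocol article*

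**What the plan says.** **Who is analysed.** The Statistical analysis section states: "The intention-to-treat analysis will be conducted if individuals are lost to follow-up". The Methods paragraph of the Abstract ties the principle to the same event: "We will manage the intention-to-treat analysis for individuals who will withdraw from this study". Neither says that every randomised participant is analysed in the assigned group whatever happens.

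**How they are analysed.** The model for primary and secondary outcomes is given as "We will use two-way repeated measures analysis of variance (group × time) to compare the effect of neuromuscular training exercise group"; the comparators are the other two arms. The software sentence reads: "Statistical analyses will be carried out using SPSS 22.0 and Microsoft Excel 2012 software". No imputation or likelihood-based method is named. Study design sets four assessments: baseline, 6 weeks, 3 months and 6 months.

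**Who leaves.** Withdrawal criteria and management says "PFPS patients will be asked or be allowed to quit the study if" one of three conditions is met. One is that "they obtain a side effect because of treatment". The section does not separate stopping the intervention from leaving the study. In the Abstract, "The primary outcome measures include the adverse events, visual analog scale for pain, and Anterior Knee Pain Scale Index" are listed together, so a treatment-related adverse event is both a primary outcome and a route out of the trial.

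**The concern.** Intention-to-treat defines the analysis set: everyone randomised, in the arm assigned. It is not a remedy that is switched on when someone is lost. Stated conditionally, it leaves open what rule applies to a participant who attends every visit but stops exercising or taping.

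The named model also sits badly with the promise. Repeated-measures ANOVA, as usually run in SPSS, works on participants with a value at every time point. The people for whom intention-to-treat is invoked are those it would leave out, unless their missing values are filled in first.

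The withdrawal rule adds a possible link between treatment, outcome and loss. If a participant with a side effect leaves the study entirely, one primary outcome event can end collection of the other two, the VAS and the AKPS. The three arms differ in exposure: exercise and taping involve three attendances a week, health education one session a week. Losses could therefore differ by arm, and a comparison among completers would then no longer be the comparison that randomisation set up.

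**Working it through.** **The plan's own figure.** The article gives no dropout rate. Its only relevant number is the minimum of 60 (20 per group) in Sample size estimation, with no stated allowance for loss. The inputs given there (f = 0.3, alpha = 0.05, power = 0.95, 3 groups, 3 measurements) do not include the correlation between measurements or the type of effect tested. They give 60 for a within-subject test at correlation 0 and for a group × time test at correlation 0.2, but other values elsewhere. The figure is neither confirmed nor refuted, and this point does not depend on it. It serves below only as a base. Study design mentions 120 patients; the percentages below apply to either total.

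**Step 1. Participants left with complete records.** Assumption: a fraction q misses each of the three post-baseline visits, independently. Complete share = (1 − q)³.

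| q | Complete share | Of 60 |
|---|---|---|
| 5% | 0.95³ = 0.857 | 51.4 |
| 10% | 0.90³ = 0.729 | 43.7 |

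If instead the same people miss everything (whole-person dropout of 5% or 10%), 60 × 0.95 = 57 or 60 × 0.90 = 54 remain. Independence is thus the less favourable of the two patterns.

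**Step 2. Collected data that would be discarded.** Under the same independence assumption, assessments collected per participant = 1 + 3(1 − q), and assessments used by a complete-case analysis = 4(1 − q)³.

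- q = 5%: collected 3.85 × 60 = 231; used 4 × 0.857 × 60 ≈ 206; discarded ≈ 25 (11%).
- q = 10%: collected 3.70 × 60 = 222; used 4 × 0.729 × 60 ≈ 175; discarded ≈ 47 (21%).

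A mixed model would use all 231 or 222. Under whole-person dropout straight after baseline, the only discarded data would be the baseline values of those lost.

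**Step 3. Shift if exits are informative.** If a share s of one arm leaves and would have scored d points worse than those who stay, the completers' mean for that arm looks s × d too good. With s = 0.20 and d = 1.5 VAS points, both assumed: 0.20 × 1.5 = 0.3 points on the 0–10 scale. With s = 0.10 it is 0.15.

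A deliberately extreme simulation (two arms of 20, no true difference, exactly the worst 4 of 20 leave one arm) shifted the completer comparison by 0.34 SD. It raised the t-test false-positive rate from about 5% to about 20%. This is the worst pattern for a 20% loss in one arm, not a forecast.

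**Step 4. What each remedy reaches.** A mixed model addresses Steps 1 and 2, and is valid if missingness depends only on observed data. It does not by itself cure Step 3 when exit depends on unobserved scores. Continued assessment after the intervention stops addresses Step 3 at source. Both are needed.

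**The case against.** The best defence is that the article states an intention to keep withdrawn participants in the analysis and leaves the method to a fuller document. A repeated-measures ANOVA on imputed data would include everyone randomised. That is fair, and the missing-data method alone would not be a finding. What remains is what the article does fix: a conditional rule, stated twice in similar terms, and a model that meets the rule only with an unstated addition.

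A reader might also infer several stronger things that the documents do not support:

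- *That the ANOVA cannot include lost participants.* The article does not say so. Deletion of incomplete cases is a property of the standard procedure, and imputation could avoid it.
- *That non-adherent participants are excluded.* Nothing excludes them, and no per-protocol set is defined. The rule is left open, not set against them.
- *That participants with side effects are removed and their later scores never collected.* The wording is that they are asked or allowed to quit. The article is silent on assessment afterwards.
- *That the bias favours exercise.* The limitations paragraph concedes that the exercises may not suit everyone, especially those in high pain, which is some support. But adverse events are expected from taping too, both active arms attend three times a week, a VAS score above 8 is an exclusion, and no side-effect rates are given.

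The objection that every rate used above is invented is also correct. The arithmetic shows how the mechanism scales, not what will happen in this trial.

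**Conclusion.** The point holds in a limited form. Intention-to-treat should not depend on whether anyone is lost. The stated model in its standard form does not deliver it without imputation, and would discard the earlier visits of anyone with a gap. The withdrawal wording permits loss related to treatment and outcome, because it speaks of leaving the study and does not say that assessment continues.

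The size is not known. The figures of 51 to 44 complete out of 60 rest on assumed missing rates of 5–10% per visit and independence between visits. The 0.3-point VAS shift rests on an assumed 20% exit from one arm and an assumed 1.5-point deficit. The direction of any bias cannot be stated from the article. Assessments that are not made cannot be recovered later. The article reports recruitment still in progress, so the follow-up wording is the more urgent part.

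**What to change.** 1. Replace the conditional sentence, in the Statistical analysis section and in the Abstract, with an unconditional one: all randomised participants are analysed in the group to which they were assigned, whatever their adherence or completeness of follow-up.
2. Replace the repeated-measures ANOVA with a linear mixed model for repeated measures (SPSS MIXED), with group, time and their interaction, using every available visit. State that it assumes data are missing at random.
3. Leave the clinical withdrawal criteria as they are, but separate stopping the assigned intervention from leaving the study. Say that anyone who stops the intervention is still invited to the remaining 6-week, 3-month and 6-month assessments unless they withdraw consent for follow-up.

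The cost is a few sentences in the analysis and withdrawal sections and a few extra contacts on the existing schedule. No new visits or measurements are needed.
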